### Study Population

#### Inclusion Criteria

Eligible infants are full-term (gestational age ≥37 weeks), healthy, singleton infants aged 4-6 months whose birth weight was ≥2500 g.

#### Exclusion Criteria

Infants with any underlying or chronic diseases, those with a known case of, or recovery from, protein-energy malnutrition, and infants regularly receiving medication except mineral and vitamin supplementation will be excluded.

### Participant Selection and Recruitment

Parents or caregivers of infants aged 4-6 months who are eligible for the study will be approached by a researcher when they routinely visit the well-baby clinic and asked if they are interested in taking part in the study. The researcher will give the parent an information sheet and answer all queries on a case by case basis. If they consider participating, contact details will be obtained. After 48 hours, the researcher will call the parents to ask if they wish to take part and, if they agree, the first appointment will be scheduled. At the first visit, informed consent will be signed by the parent or legal guardian who is the primary caregiver of the participant.

### Data Collection

There are 3 visits at the well-baby clinic for each participant when they are 6, 9, and 12 months of age (Table 1).

**Table 1 table1:** Data and collection of biological samples.

Data collection	First visit, age 6 months	Second visit, age 9 months	Third visit, age 12 months
Demographic data	Family type, family income (monthly), primary caregiver Parental education and occupation Parental body weight and height Prenatal screening and problems Mode of delivery, gestational age at birth, birth weight, length, and head circumference Postnatal problems (eg, neonatal jaundice)	N/A^a^	N/A
Milk feeding	Type of milk feeding, duration of exclusive breastfeeding	Type of milk feeding, duration of breastfeeding/using breast milk	Type of milk feeding, duration of breastfeeding/using breast milk
Dietary intake	Age of first introduction of complementary feeding, type of first complementary feeding, age of introducing each type of diet (cereal, meat, egg, milk) 24-hour dietary recall Food Frequency and Baby Eating Behavior Questionnaire	Age of introducing each type of diet 24-hour dietary recall 3-day food record Food Frequency and Baby Eating Behavior Questionnaire	Age of introducing each type of diet 24-hour dietary recall 3-day food record Food Frequency and Baby Eating Behavior Questionnaire
Anthropometric measurements	Bodyweight, length, head circumference, mid-upper arm circumference	Bodyweight, length, head circumference, mid-upper arm circumference	Bodyweight, length, head circumference, mid-upper arm circumference
Biological sample collection	N/A	N/A	Blood sample: 5 ml venous blood Body composition: 1.5 mL urine × 3 samples, before and after dosing with Deuterium oxide
Other information	Feeding problems, acute illness	Feeding problems, acute illness	Feeding problems, acute illness

^a^N/A: not applicable.

### Biological Sample Collection, Preparation, and Storage

#### Blood Samples

At 12 months of age, a venous blood sample will be obtained by experienced nurses or health professionals. Five milliliters of venous blood will be separated into 4 collecting tubes; 1 EDTA tube for ESR and plasma amino acids, 1 EDTA microtainer for complete blood count (CBC), 1 clotted blood tube for growth hormone, IGF-1, IGFBP-3, and 1 heparinized microtainer for serum ferritin, serum iron, and serum total iron-binding capacity. The blood samples for CBC, ESR, serum ferritin, serum iron, and total iron-binding capacity will be analyzed on the day of blood collection. The rest of the blood samples for growth hormone, IGF-1, IGF-binding protein 3 (IGFBP-3), and plasma amino acid analysis will be centrifuged and aliquoted into cryovials within the same day and stored at –80^o^C until analysis.

#### Urine Samples

Infant body composition will be measured by the isotope dilution technique using deuterium oxide (^2^H_2_O). At 12 months of age, the dose of deuterium oxide calculated according to infant body weight (0.1 g per kg ^2^H_2_O body weight) will be prepared as a solution (in water, juice, or milk) and orally administered to infants during their final visit. Urine samples will be obtained before dosing and after dosing at 6 and 24 hours. Urine samples will be stored at –80^o^C until analysis.

### Study Outcomes

#### Primary Outcome

The primary outcome measure will be the conditional change of growth parameters (WAZ, WLZ, LAZ) from 6-12 months of age.

#### Secondary Outcomes

Secondary outcome measures will be (1) the conditional change of BMIZ from 6-12 months of age, (2) anthropometric measurements at 12 months of age, (3) infant body composition at 12 months of age, (4) iron status including CBC, serum ferritin, SI and total iron-binding capacity at 12 months of age, (5) growth-related hormones (growth hormone, IGF-1, IGFBP-3) at 12 months of age, and (6) plasma amino acids at 12 months of age.

### Outcome Measures

#### Energy and Nutrient Intake

Dietary data will be collected using 24-hour dietary recalls and the Food Frequency Questionnaire at 6, 9, and 12 months and 3-day food records at 9 and 12 months. All dietary data will be converted to energy and nutrient intake (ie, carbohydrate, fat, protein, calcium, phosphorus, iron, zinc, vitamin B1, vitamin B2, vitamin C, and vitamin A) by using the Institute of Nutrition Mahidol University Calculation program version 4.0 developed by the Institute of Nutrition, Mahidol University, Bangkok, Thailand [26]. This program reports total protein and iron intake from both animal and plant sources. Breastfeeding will be recorded as frequency and duration (minutes per meal) each day, then the volume of breast milk will be estimated using the average amount from two algorithms [27,28].

#### Anthropometric Assessment

Bodyweight will be measured using calibrated electronic scales accurate to 0.01 kg and recumbent length using a standard wood board accurate to 0.1 cm. The SD z-scores for weight-for-age, length-for-age, weight-for-length, and BMI will be calculated using WHO software (WHO Anthro version 3.2.2) based on the 2007 WHO Growth Standard [29]. Although the WHO recommends weight-for-length to be used to determine wasting and overweight for children aged <2 years, a recent study showed that infant BMI had a higher positive predictive value than weight-for-length for childhood obesity [30].Therefore, the present study will measure both indices.

### Dietary Data Collection Tools

The format of the 24-hour dietary recalls and 3-day food records have been adapted from Lanigan et al [27] and translated into the Thai language by the researcher who is a Thai native speaker. The semi-quantitative Food Frequency Questionnaire was developed with information on food items consumed by Thai infants and toddlers aged 0-3 years relating to the food consumption data of Thailand 2016 [31]. The Food Frequency Questionnaire contains 130 food items. Appetite traits will be evaluated by the Baby Eating Behavior Questionnaire, which was developed by Llewellyn et al from the Gemini birth cohort [32].

### Laboratory Analyses

#### Infant Body Composition

Urine samples will be measured by isotope-ratio mass spectrometry (Gasbench-Delta XP system, Thermo Fisher Scientific, Bremen).

#### Iron Status

CBC will be analyzed by using an automated hematological analyzer (Sysmex XN 9103, Sysmex UK). An automated system will be used for the direct determination of ESR (VES-MATIC cube 30, DIESSE Diagnostica Senese). Serum ferritin, serum iron, and total iron-binding capacity will be analyzed by using a chemiluminescent method (Cobas modular analyzer, Roche Diagnostics, F Hoffmann-La Roche, Germany).

#### Growth-Related Hormones

Growth hormone, IGF-1, and IGFBP-3 will be analyzed by enzyme-linked immunosorbent assay (IMMULITE 2000, Siemens Healthcare Diagnostics Products).

#### Plasma Amino Acids

Twenty plasma amino acids will be analyzed by using the high-performance liquid chromatography (Biochrom30 amino acid analyzer, Biochrom).

### Statistical Analysis

There are two main parts of the statistical analysis. First, we will summarize the population characteristics of milk feeding, complementary feeding, and prevalence of undernutrition, overweight/obesity, and iron deficiency. Second, we will examine the associations between protein intake and source during complementary feeding and the outcomes specified in the objectives and hypotheses. All statistical tests will be considered significant when the *P* value is <.05 or 95% CIs of odds ratios do not include 1.

Descriptive data will be presented as mean (SD), median with interquartile range, or percentages depending on data type and distribution. These data will include demographic characteristics of infants and families, breastfeeding rate, age of the first introduction of complementary feeding, details of complementary feeding and energy/nutrient intake at each time point, average growth parameters at each time point, growth trajectory, and the prevalence of malnutrition (including wasting, stunting, overweight/ obesity, iron deficiency, iron deficiency anemia).

Protein intake at each time point, both total and separated by dietary source (ie, dairy protein, nondiary animal-based protein, and plant-based protein), will be considered as primary predictors to examine associations between protein intake and outcomes. To investigate associations between those predictors and continuous outcomes such as growth z-scores, percentage of body fat/fat-free mass, and blood parameters, we will use linear regression and correlation models (Pearson or Spearman correlation) for either univariate or multivariate analysis. For multivariate analysis, covariates will be selected for each of the dependent outcomes from previous research publications and our univariate analyses. Additionally, we intend to apply the directed acyclic graphs identifying covariates to reduce confounders [33]. If the dependent outcomes are categorical data such as nutritional status or iron status, binary or logistic regression analysis will be used as the main models.

The study aims to reduce the bias of baseline body size of individual infants on growth outcomes by using conditional growth. This method captures how an individual child deviates from the average growth trajectory in the population, taking into account overall regression to the mean, and expresses growth acceleration or deceleration in an individual relative to this population growth pattern. For example, if the conditional weight z-score is positive, we can interpret that the infant has shown more rapid weight gain than others in the population who had the same baseline size [34]. Therefore, the conditional change in growth parameters from 6 to 12 months will be calculated using linear regression of weight/length z-scores at 12 months on baseline values at 6 months. Residuals from the model represent the difference between observed and predicted growth over this period.

We will use data from the standard recommendations, previous research, and our own data to determine the most appropriate cut-offs for low or high protein intake. We will then compare the outcomes between these groups.

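### Three primary outcomes, four primary protein predictors and three ages give 36 unranked tests, each judged at P<.05, so a primary claim does not carry a 5% error rate

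*Protocol article*

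**What the plan says.** Under Primary Outcome, the protocol article gives three growth indices equal standing: "The primary outcome measure will be the conditional change of growth parameters (WAZ, WLZ, LAZ) from 6-12 months of age".

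Under Statistical Analysis, the exposures are "Protein intake at each time point, both total and separated by dietary source", the sources being dairy, nondairy animal and plant. All of these "will be considered as primary predictors to examine associations between protein intake and outcomes". Data Collection sets the ages: "There are 3 visits at the well-baby clinic for each participant when they are 6, 9, and 12 months of age". Energy and Nutrient Intake confirms that diet is assessed at each of them.

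The decision rule, also under Statistical Analysis, is "All statistical tests will be considered significant when the *P* value is <.05 or 95% CIs of odds ratios do not include 1". The article names no lead outcome, predictor or age. It gives no adjustment or testing order, and it does not describe the growth analyses as exploratory.

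**The concern.** A protocol that is silent on multiplicity may leave it to the analysis plan. This one is not silent: it sets one unadjusted threshold and applies it to all tests, including every pairing of outcome and predictor that it calls primary. Any of those P values below .05 could then be reported as a positive primary result.

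This matters because Aims and Hypotheses presents hypotheses to be tested, and the abstract's conclusions expect the results to help inform complementary feeding recommendations. A statement that protein from a given source is associated with infant growth would be read as carrying a 5% error rate. Under the stated rule, that rate applies to each test alone and not to the set from which the result was picked.

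**Working it through.** **Inputs from the protocol article**
- Outcomes: 3 (Primary Outcome).
- Predictors: 4 (Statistical Analysis).
- Ages: 3 (Data Collection; Energy and Nutrient Intake).
- Threshold: .05 per test, taken as two-sided because sidedness is not stated.
- Completers: 150 - 4 = 146 (Results).
- Sample size: 0.5 SD difference, SD 1.0, 80% power, alpha .05, giving 126, or 148 with 15% dropout (Sample Size Calculation).

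**The plan's own figure.** n per group = 2(1.960 + 0.842)^2 / 0.5^2 = 62.8, so 63 per group and 126 in total. 126/0.85 = 148.2. The stated sample size is reproduced, and it spends the full .05 on each of the three outcomes. Its contrast, frequent versus less frequent red meat, is not one of the four protein predictors, so it supplies no lead hypothesis for them.

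**Count.** 3 x 4 x 3 = 36. This is a minimum. Univariate and multivariate versions, correlation as well as regression, and the low/high protein groups with cut-offs drawn partly from the study's own data all add tests on the same outcomes.

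**Expected false positives if no association exists.** 36 x .05 = 1.8. Correlation between tests does not change this.

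**Chance of at least one false positive, same condition, independent tests.** 1 - 0.95^k:

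| Family | k | Chance |
|---|---|---|
| All pairs | 36 | 84% |
| Without total protein (the sum of the sources) | 27 | 75% |
| Without 6-month intakes | 24 | 71% |
| Three outcomes counted as two | 18 | 60% |
| Fewest tests exceeding 50% | 14 | 51% |
| One predictor at one age, three outcomes | 3 | 14% |

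**Correlated tests.** The 36 tests are not independent: total protein is the sum of its sources, weight-based indices overlap, and intakes repeat within infants. The documents give no correlations, so all those below are assumptions. The simulation used 146 infants, no true association, total equal to the sum of three sources, 36 univariate correlation tests and 4,000 runs per scenario. Correlations between sources were -0.2, 0 and 0.3.

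| Assumed outcome correlations | Age-to-age intake correlation 0 to 0.7 | 0.9 |
|---|---|---|
| .3, .3, 0 | 63-79% | 54-59% |
| .75, .6, .05 | 57-73% | 46-51% |
| .9, .7, .4 | 52-70% | 41-47% |
| .9 throughout | 43-60% | 37-39% |

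The chance exceeded 50% in 48 of 60 scenarios. Most of the other 12 had an age-to-age correlation of 0.9; the rest had all outcomes correlated at .9 and intakes correlated at 0.5 or more between ages.

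**Cost of a stricter threshold.** Power for a 0.5 SD difference between equal groups is Phi(0.5 x sqrt(n/2) - z), with n per group. The detectable correlation at 80% power and 146 infants is tanh[(z + 0.842)/sqrt(143)].

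| Threshold | z | Power, 126 | Power, 146 | Detectable r |
|---|---|---|---|---|
| .05 | 1.960 | 80% | 86% | 0.23 |
| .05/3 = .0167 | 2.394 | 66% | 73% | 0.26 |
| .05/9 = .0056 | 2.773 | 51% | 60% | 0.29 |
| .05/36 = .0014 | 3.197 | 35% | 43% | 0.33 |

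These are the strictest steps. Holm relaxes the threshold after each rejection.

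**The case against.** **This is a cohort examining associations.** No treatment or licensing claim rests on one P value, and the Discussion says the results may be used to plan a later intervention study. Formal error control is less strictly expected here than in a confirmatory trial. This stands and lowers the severity. It does not rescue the rule, because the article itself uses the label primary and a yes/no significance threshold.

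**Multiplicity belongs in the analysis plan, and .05 is only a conventional threshold that adjusted P values could also meet.** This is partly fair. But the sentence covers all tests and mentions no adjustment, so read as written it fixes an unadjusted rule.

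**The percentages assume that nothing is associated with anything.** This is correct, and the Introduction cites evidence that protein does affect growth. A reader might infer that any significant primary finding is more likely than not to be false. The documents do not support that: the figures give the chance of at least one false positive when no association exists, not the chance that a given positive result is wrong. Nor should 84% be quoted alone, since it requires independence.

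**The mechanism aim.** A reader might also multiply "Twenty plasma amino acids will be analyzed" by three hormones and charge the plan with 60 further tests. The article plans no such grid. The hypothesis concerns essential amino acids, a subset; the abstract's objective speaks of exploring the pathway; and these measures are secondary outcomes. That count should not be used.

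**Conclusion.** The concern holds as a point that should be fixed. The count of 36 unranked primary tests at .05 comes directly from the text, and 1.8 expected false positives under no association follows whatever the correlation. The chance of at least one is roughly 50-80% under assumed correlations, with 84% as the independence value and about 40% at very high correlation. More likely than not is therefore a conditional statement: it needs the absence of any true association and correlations short of the extremes. At every setting tried, the chance was at least 37%, far above 5%. The unadjusted rule therefore cannot support a primary claim at the 5% level.

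**What to change.** Replace the sentence that applies P<.05 to all tests with one of these:

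1. **Control multiplicity across the primary family.** Either apply Benjamini-Hochberg to all 36 tests, or name a small lead set that keeps the animal, dairy and plant contrast, apply Holm over WAZ, WLZ and LAZ, and make the remaining combinations secondary. A single predictor at a single age would not answer the first objective, which concerns both amounts and sources.
2. **Declare the 36 associations exploratory.** Report all estimates with 95% CIs and make no significance claims.

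In either case, label the amino-acid and hormone associations exploratory, with false discovery rate control if their P values are interpreted.

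Date the change. The Results section says data collection finished in May 2019, and the abstract says data analyses were under way. The amendment should therefore say that it was made after data collection but before the outcome models were run. If some models had already been run, it should say which, and option 2 is then the safer choice.

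**Cost.** The change affects wording and analysis only; no new data are needed. Option 1 costs power. With one lead contrast tested on three outcomes, the strictest Holm step is .0167. The detectable correlation at 146 infants then rises from 0.23 to about 0.26. Power for a 0.5 SD two-group difference falls from 80% to about 66% at 126 infants, and is about 73% at 146. If three source predictors at one age were tested together on the three outcomes (nine tests), the strictest step would be .0056, with about 51% and 60%, so the lead set should be small. Option 2 costs no power but gives up any confirmatory claim.

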**Results:**

The recruitment of study participants and data collection was undertaken from June 2018 to May 2019. Data and laboratory analyses are ongoing and are expected to be completed by December 2020. A total of 150 participants were enrolled, and 146 completed the study. We hypothesized that protein intake from animal-sourced foods in recommended quantities could support normal weight and length gain and lower the risk of undernutrition associated with similar amounts of plant-based protein. However, higher protein intake, especially from milk protein, may be linked to increased body fat via plasma amino acids and the growth hormone-IGF axis.

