### Aims and Hypotheses

We aim to understand the impact of dietary protein in early life using a holistic approach. This study will fill some of the knowledge gaps related to underlying mechanisms through the following objectives and hypotheses:

We will investigate the associations between the amounts and sources of dietary protein typically provided to Thai infants aged 6 to 12 months and changes in growth, including weight-for-age z-score (WAZ), weight-for-length z-score (WLZ), length-for-age z-score (LAZ), and BMIZ over 6-12 months. We will test the hypothesis that protein intake from animal-sourced foods in recommended quantities can support normal weight and length gain and reduce the risk of undernutrition associated with similar amounts of plant-based protein.We will investigate the associations between the amounts and sources of dietary protein typically provided to Thai infants aged 6 to 12 months and body composition at 12 months of age. We will test the hypothesis that a higher intake of protein from animal-sourced foods, especially dairy protein, is associated with an increased proportion of body fat during infancy.We will investigate the associations between complementary foods that provide different amounts of protein from animal-sourced foods and plant-based diets typically provided to Thai infants aged 6 to 12 months with iron status at 12 months of age. We will test the hypothesis that the timely introduction of protein from animal-sourced foods, especially red meat in the recommended amount, is associated with improved iron status and lower risk of iron deficiency anemia, without increasing the risk of overweight/obesity.We will investigate the possible mechanisms linking dietary protein and growth in early life through metabolomic processes. We will test the hypothesis that high protein intake from animal-sourced foods is associated with increased plasma essential amino acids, which may be correlated with concentrations of growth hormone, IGF-1, and IGFBP-3.

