### Definitions

Key terms are defined in Textbox 1.

Definitions.*Complementary feeding* is all solid and liquid foods other than breast milk or infant and follow-on formula, as suggested by the European Food Safety Authority (EFSA) [21] and the position papers from the European Society for Pediatric Gastroenterology Hepatology and Nutrition [22].*Stunting* is defined as LAZ <2 SD below the median of the WHO growth standards for children aged under 5 years [23].*Wasting* is defined as WLZ <2 SD below the median of the WHO child growth standards for children aged under 5 years [23].*Underweight* is defined as WAZ is <2 SD below the median of the WHO child growth standards for children aged under 5 years [23].*Overweight* is defined as WLZ >2 SD above the median of the WHO child growth standards for children aged under 5 years [24].*Obesity* is defined as WLZ >3 SD above the median of the WHO child growth standards for children aged under 5 years [24].*Iron deficiency* is defined by at least one of the following serum ferritin less than 12 μg/L (if erythrocyte sedimentation rate, ESR ≤10 mm/h) or serum ferritin less than 30 μg/L (if ESR >10 mm/h) or serum transferrin saturation less than 16% [25].*Iron deficiency anemia* is defined as iron deficiency plus hemoglobin <11.0 g/dL [25].*Exclusive breastfeeding* means the infant receives only breast milk without anything else except for water and necessary medication.*Predominant breastfeeding* means that breast milk is more than 50% of daily milk intake after 6 months of age.*Predominant formula feeding* means that infant or follow-on formula provides more than 50% of daily milk intake and for a longer period than breastfeeding.*Animal-sourced food* is defined as any food that is edible and originates from animals such as milk, dairy products, meat (ie, beef, pork, poultry), processed meats, fishes, insects, and eggs.*Plant-based protein* is defined as dietary proteins that are edible and originate from plants such as cereals, lentils, legumes, nuts, and vegetables.The *primary caregiver* is defined as the person who spends the most time looking after the infant on a daily basis.

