## Results

Recruitment commenced in June 2018 and was completed in October 2018. Data collection was completed in May 2019. Laboratory analyses are ongoing and are expected to be complete by December 2020. Initially, 150 infants were enrolled, and only 4 (3%) had dropped out at the end of the data collection period. The results of this study will be presented and disseminated through peer-reviewed journals and academic conferences.

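### Adjusted logistic regression is the main model for WHO growth categories, but at least one of wasting and overweight, and probably obesity, may have too few cases among 146 infants to support it

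*Protocol article*

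**What the plan says.** In the protocol article, Statistical Analysis, continuous outcomes go to linear regression and correlation. For categorical outcomes, with nutritional status and iron status as the examples, "binary or logistic regression analysis will be used as the main models". The main predictors are protein intake at each visit, in total and split into three sources. Covariates come from the literature and from the study's own univariate analyses, with directed acyclic graphs as an addition. A result counts as significant if P is below .05 or the 95% interval of the odds ratio leaves out 1.

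Two hypotheses in Aims and Hypotheses call on these models. Hypothesis 1 says that animal-sourced protein will "reduce the risk of undernutrition associated with similar amounts of plant-based protein". Hypothesis 3 expects better iron status with no rise in overweight or obesity.

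Under Definitions, stunting "is defined as LAZ <2 SD below the median of the WHO growth standards". Wasting, underweight and overweight use the same 2 SD distance on their own indices, and obesity uses 3 SD. Eligible infants are full-term and "healthy, singleton infants aged 4-6 months whose birth weight was ≥2500 g". The Exclusion Criteria remove "those with a known case of, or recovery from, protein-energy malnutrition". On numbers, the abstract reports: "A total of 150 participants were enrolled, and 146 completed the study".

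**The concern.** A category cut at 2 SD of a growth standard is rare in a population close to that standard, and 146 infants is a small base for a rare outcome. With few cases spread over three protein-source terms and several covariates, standard logistic regression tends to overstate odds ratios, give very wide intervals, and sometimes fail to converge or separate. Picking covariates from univariate results in the same data adds instability.

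The decision rule makes this matter in both directions. An interval that excludes 1 could be a sparse-data artefact and be read as support for hypothesis 1. An interval that includes 1 for overweight or obesity could be read as the reassurance that hypothesis 3 seeks, when the study had little chance of detecting harm.

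**Working it through.** **The plan's own figure.** Sample Size Calculation uses a difference of 0.5 SD, SD 1.0, 80% power and a .05 level (two-sided assumed). Per group: 2 × (1.96 + 0.84)² × 1.0² / 0.5² = 62.8, so 63, and 126 in total, as stated. With 15% dropout: 126 / 0.85 = 148.2, as stated after rounding. With 146 completers split 73 and 73, power for 0.5 SD is about 86%. This calculation covers mean differences in continuous z-scores and gives no support to the binary models.

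**Expected cases.** Inputs are N = 146 (Results), the cut-offs in Definitions, and the SD of 1.0 from Sample Size Calculation. The mean z at 12 months is not given, so −1 to +0.5 is assumed, with a normal distribution. For mean m, cases below −2 are 146 × Φ(−2 − m), cases above +2 are 146 × [1 − Φ(2 − m)], and cases above +3 are 146 × [1 − Φ(3 − m)].

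| Assumed mean z | Below −2 | Above +2 | Above +3 |
|---|---|---|---|
| −1 | 23.2 | 0.2 | 0.0 |
| −0.5 | 9.8 | 0.9 | 0.03 |
| 0 | 3.3 | 3.3 | 0.2 |
| +0.5 | 0.9 | 9.8 | 0.9 |

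Wasting and overweight are opposite tails of one index, weight-for-length. If its mean is 0 or higher, the lower tail is at most 146 × 0.0228 = 3.3 cases. If the mean is 0 or lower, the same limit holds for the upper tail. With SD 1.0, one of the two therefore has no more than about 3.3 expected cases whatever the mean.

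**Events per model term.** The three source terms are in the plan. The number of covariates is not, so five are assumed, giving eight terms.
- 3.3 cases: 3.3/3 = 1.1 and 3.3/8 = 0.4.
- 9.8 cases: 9.8/3 = 3.3 and 9.8/8 = 1.2.
- 23.2 cases: 23.2/3 = 7.7 and 23.2/8 = 2.9.

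**Behaviour of standard fits with continuous predictors.** This simulation used N = 146, independent standardised predictors, one of them with a true odds ratio of 1.5 per SD, eight terms, and 400 runs per setting. Power is among fits that succeeded.

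| Prevalence | Failed or separated | Mean log odds ratio / truth | Middle 80% of odds ratios | Power |
|---|---|---|---|---|
| 2.3% | 21% | 1.53 | 0.67 to 6.25 | 10% |
| 5% | 0.5% | 1.32 | 0.90 to 3.27 | 17% |
| 10% | 0% | 1.15 | 1.07 to 2.61 | 31% |
| 15% | 0% | 1.03 | 1.08 to 2.19 | 39% |

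With only the three source terms at 2.3%, 4.5% of fits failed and the ratio was 1.17.

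**A two-group comparison.** The plan also intends to compare low and high protein groups. An even split of 73 and 73 is assumed here, without adjustment. At the null, SE(log OR) = √[4 / (events × (1 − p))].
- p = 2.3%: √[4 / (3.36 × 0.977)] = 1.10, and the 95% interval runs a factor exp(1.96 × 1.10) ≈ 8.7 either side.
- p = 5%: √[4 / (7.3 × 0.95)] = 0.76, factor 4.4.
- p = 10%: √[4 / (14.6 × 0.90)] = 0.55, factor 2.9.

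For a true odds ratio of 2, Wald power is 0.1%, 3.7% and 18%, and the chance that one group has no case is 39%, 8.6% and 0.5%. At 10% prevalence, even an odds ratio of 6 gives only 69% Wald power.

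**The case against.** Several points on the other side are sound.

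- **The event count is assumed.** The article states no prevalence. Eligibility removes only known or recovering malnutrition and sets no z-score limit at entry, and undernutrition can develop between 6 and 12 months. A reader might infer that these infants are screened free of malnutrition, so that every category must be nearly empty. The criteria do not say that. The Introduction describes childhood stunting in Thailand as falling only slowly. A mean length-for-age z of −1, or pooling of the undernutrition categories, could give 20 or more cases.
- **The estimator is not named.** The text does not specify ordinary maximum likelihood or Wald intervals, and Firth regression is a form of logistic regression. A full analysis plan might add it. Even so, the article settles the main model, the way covariates are chosen and the decision rule, and their combination suits sparse categories poorly.
- **The main predictors are quantities.** The 73 and 73 split and the empty-group rates apply only to the low/high comparison. The simulation with continuous predictors is the closer match, and there outright failure is confined to the lowest prevalence.
- **The primary outcome is continuous.** Conditional change in three z-scores is primary, and growth categories are not among the listed primary or secondary outcomes. This limits the weight of the point. Hypotheses 1 and 3 nevertheless speak of risk.

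What does not fall away is the weight-for-length result: moving the mean fills one tail only by emptying the other.

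**Conclusion.** The concern holds in a conditional form. Given SD 1.0 and approximate normality, at least one of wasting and overweight has about 3 expected cases or fewer, and obesity has fewer than one in every scenario tabulated (it would need a mean well above +0.5 to do better). Standard adjusted odds ratios for such categories may be inflated by up to about 1.5-fold on the log scale with eight terms, and about one fit in five may fail at 2.3% prevalence. Instability lessens through 5% and 10%, and bias is small by 15%.

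A reader might infer that logistic regression is unusable for all the binary outcomes, or that the study's main result is at risk. The article supports neither. Stunting or pooled undernutrition may have enough cases. Iron deficiency falls under the same sentence, but the Introduction describes it as highly prevalent in Thailand. The primary analysis keeps about 86% power for 0.5 SD, given an even split.

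The size of the problem rests on the assumed mean z, on the SD of 1.0 carrying over to the 12-month sample, and on the assumed number of covariates. A larger SD would add cases in both tails. The point merits a change to the analysis wording but does not undermine the design.

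**What to change.** For the growth categories defined by WHO cut-offs:

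1. Name Firth penalised logistic regression with profile-likelihood intervals as the method when events are few.
2. In those models, limit terms to the exposure and one or two covariates chosen from the directed acyclic graph, not from univariate results. Follow-up is complete, so the case count per category can be tabulated without reference to protein intake and the number of terms fixed before any model is fitted.
3. Base the growth conclusions, including the growth part of hypothesis 1, on the continuous conditional z-scores that are already primary.
4. Report very sparse categories as counts and percentages only.
5. State that an overweight or obesity interval including 1 will not be taken as evidence of no increased risk.

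The iron-status models need no change if deficiency proves common.

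The cost is a few sentences and a standard software option, with no new data. The price is less covariate adjustment in the sparse models, hence more room for confounding. Firth estimation reduces bias and handles separation but does not restore power, so items 3 to 5 are needed as well as item 1.
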